### Data analysis

#### Secondary data

As the current COVID-19 pandemic had a considerable effect on influenza vaccination rates and at least on pneumococci vaccination rates, too, it is important to differentiate between a baseline before the pandemic and a baseline during the pandemic. The alterations in vaccination rates due to the pandemic will be determined by using the Interrupted Time Series Models (ITS).

After the determination of the baselines, pre-post comparison analyses will be conducted for both outcomes differentiated by intervention and control group. The pre-post comparisons will be conducted by performing comparisons of means based on two-sided tests with significance levels of 5%. Under consideration of clustering, various influencing factors are taken into account.

Furthermore, subgroup analyses such as for patients in nursing homes or for single vaccinations such as the pneumococci vaccination are planned. Finally, if a sufficiently high number of cases in all regions is reached, a comparing analysis of the vaccination uptake rates between the three regions will be conducted.

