## Background

With older age the prevalence of chronic conditions such as diabetes mellitus or cardiovascular problems is increasing. At the same time, the age-associated weakening of the immune system contributes to an increased incidence and severity of infectious diseases. Therefore, severe courses or life-threatening complications from infections occur more frequently with older age [1–4]. Infections such as seasonal influenza can therefore last longer or run a more severe course, with serious health risks such as pneumonia or myocarditis. In addition, the risk of secondary diseases (e.g., sepsis as a result of influenza or pneumococcal infection) is higher in patients aged 60 and older. There is also a significant increase in mortality as well as hospitalization among elderly people infected with influenza [5]. The COVID-19 pandemic also shows the increased vulnerability of people in older age to new pathogens [6, 7]. For these reasons, the uptake of existing vaccinations for patients aged 60 and older is of major relevance for preventing the aforementioned severe consequences.

In Germany, the current uptake of vaccinations that are recommended for this age group according to the Standing Committee on Vaccination (STIKO; seasonal influenza, pneumococci, herpes zoster and revaccinations against tetanus, diphtheria and pertussis) is unsatisfactory [8]. In particular, the annual influenza vaccination rate is low in the age group 60 and older (influenza season 2020/2021: 47.3%) and far from the rate of 75% recommended by the Council of the European Union [8, 9]. The rates for pneumococcal vaccination in Germany are low and vary widely between 14.8% and 40.4% depending on the region in the age group between 60 and 73 years [8]. The vaccination rate against herpes zoster in the German population over 60 years is generally extremely low, in the single digits [8].

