The focus of the summative evaluation will be on a pre-post comparison between the intervention and control group, considering differences between the two groups that already existed before the intervention. For the post analysis, GP claims data from 7 quarters after the start of the intervention are available for analysis (07/01/2022–03/31/2024). Due to the still unknown impact of the COVID-19 pandemic on the next influenza vaccination season, a period of at least 24 months prior to the start of the intervention will be considered for pre-analysis – meaning the vaccination and immunisation uptake rates achieved prior to the intervention. Because influenza vaccination should occur annually, comprehensive information on the baseline population and the number of vaccinated persons is available. The determination of vaccination uptake rates, on the other hand, is more challenging because the size of the population is unclear due to the long periods of time between booster vaccinations. Persons aged 60 and older are recommended to receive a booster vaccination against tetanus, diphtheria, and pertussis only every 10 years. A booster vaccination against pneumococci after 6 years (or later) is beneficial but not generally recommended by the STIKO. Furthermore, there is no recommendation for a booster vaccination against herpes zoster after the basic immunisation has been completed. The available data does not allow to identify if patients aged 60 and older got a booster vaccination against tetanus, diphtheria, and pertussis in the past 10 years and if patients aged older than 60 have already been vaccinated against pneumococci or herpes zoster. Therefore, we will analyse the increase in the vaccination uptake rate among participating GPs compared to non-participating GPs. Provided that the necessary number of cases is achieved, subgroup analyses for individual vaccinations (e.g., pneumococci) are planned.

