Thus, it is assumed in the following that the influenza vaccination uptake rate as primary outcome increases by 3% as a result of the intervention. This 3%-increase should be seen as an initial change. To detect this effect in the secondary data analysis with a power of 90% at a significance level of alpha = 5% (two-sided), 17,508 patients would be needed without considering the cluster effect. Based on available anonymised data from previous studies [32, 33], the intra-cluster correlation (ICC) is expected to be 0.08. With a mean cluster size of 48 patients per practice vaccinated against influenza on average, this results in a design effect of 4.76 and a corresponding required case number of 83,338 patients. Accordingly, about 1736 GPs would be needed (868 GPs in the intervention and control groups each). Likewise, an increase of 3% is also targeted for increase in vaccination uptake rate of further recommended vaccinations as the secondary outcomes. Since the assumed cluster size is reduced to 28, resulting in a design effect of 3.16 with an ICC of 0.08, a case number of 55,325 patients is required for these analyses. For this, 1976 GPs are needed according to the cluster size – 988 GPs in each of the intervention and control groups. Therefore, due to the smaller cluster size for the secondary outcome, a total of 988 GPs is required for the intervention group for the analysis. To ensure that the required number of cases will be achieved, an additional 7% (69 GPs) was added to the calculated number of cases. This resulted in a required total number of 1057 GPs per group.

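### The analysis section attaches its 5% test to pre-post comparisons split by group and names no between-arm test or primary baseline, although the design section promises a between-arm comparison

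*Protocol article*

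**What the plan says.** Two sections of the protocol article describe the analysis of the claims data.

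- *Summative evaluation: secondary data* asks whether the intervention raises vaccination rates and sets before and after rates against each other across the two groups. It puts the focus on a "pre-post comparison between the intervention and control group, considering differences between the two groups that already existed before the intervention".
- *Data analysis, Secondary data* first separates a pre-pandemic from a pandemic baseline and uses interrupted time series to estimate how the pandemic changed the rates. It continues: "After the determination of the baselines, pre-post comparison analyses will be conducted for both outcomes differentiated by intervention and control group". The next sentence gives the only stated test: "The pre-post comparisons will be conducted by performing comparisons of means based on two-sided tests with significance levels of 5" per cent. It adds that clustering and various influencing factors are considered.

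The analysis section names no between-arm test, arm-by-period term or baseline adjustment. It does not say which of the two baselines is the pre value for the influenza rate. Table 1 lists a pre-post comparison with both groups in brackets, which fits either reading. The *Sample* section sizes two equal groups.

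**The concern.** The comparison that carries the 5% level is not clearly the comparison that the study exists to make. A significant change in the intervention arm, or a significant change there and none in the control arm, is not a test of the difference between arms. The difference matters here because the analysis section itself says that the pandemic considerably affected influenza vaccination rates. A shift over time common to both arms is therefore expected, and a within-arm test cannot separate it from an effect.

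The open choice of baseline adds to this. Rates before and during the pandemic may differ, so the size of the pre-post change, and possibly the conclusion, depends on which one is used. The results feed a decision on inclusion in standard care, so the primary test should not be open to choice after the data are seen.

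**Working it through.** **Inputs from the article**
- *Sample*: "with a power of 90% at a significance level of alpha = 5% (two-sided"), intra-cluster correlation 0.08, cluster size 48, 868 GPs per arm for the primary outcome and 1057 per group after the reserve.
- Effect: "the influenza vaccination uptake rate as primary outcome increases by 3% as a result of the intervention". Whether this is absolute or relative is not stated; 3 points absolute is assumed below.
- *Background*: "the annual influenza vaccination rate is low in the age group 60 and older (influenza season 2020/2021: 47.3"%). The sample-size text gives no base rate, so p = 0.473 is an assumption.

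**Assumed, not in the article:** the pre-post correlation ρ of practice rates, and the size of the common trend.

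**The plan's own figures.** Design effect 1 + 47 × 0.08 = 4.76. 17,508 × 4.76 = 83,338. 83,338 / 48 = 1736 GPs, or 868 per arm. These reproduce. The starting figure of 17,508 does not: 3 points absolute from 47.3% needs 11,666 patients in total. That is a separate matter, and nothing below uses 17,508.

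**1. Within-arm test, no intervention effect, common trend**

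Variance of a practice rate: v = p(1 − p) × 4.76 / 48 = 0.2493 × 0.0992 = 0.0247.

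SE of the pre-post change in one arm: √(2v(1 − ρ)/G). With G = 868 and ρ = 0.5: √(0.0247/868) = 0.00534, or 0.534 points.

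- Trend 1 point: 1/0.534 = 1.87; Φ(1.87 − 1.96) ≈ 0.47.
- Trend 2 points: 2/0.534 = 3.75; Φ(3.75 − 1.96) ≈ 0.96.

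Chance that the intervention-arm test is significant with no effect:

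| GPs per arm | ρ | no trend | 1 point | 2 points |
|---|---|---|---|---|
| 868 | 0.3 | 5% | 35% | 89% |
| 868 | 0.5 | 5% | 47% | 96% |
| 868 | 0.7 | 5% | 68% | 99.8% |
| 1057 | 0.3 | 5% | 42% | 94% |
| 1057 | 0.5 | 5% | 54% | 98.5% |
| 1057 | 0.7 | 5% | 76% | about 100% |

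The pattern of intervention arm significant and control arm not has, at 868 GPs, ρ = 0.5 and a 1-point trend, probability 0.466 × (1 − 0.466) = 0.25, still with no effect.

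A second set of assumptions points the same way. Take about 101 patients per practice (48 / 0.473), a year-to-year correlation of 0.8 in the practice component, and 1057 practices:
- variance 0.2493 × (0.08 + 0.92/101) = 0.0222
- covariance 0.2493 × 0.08 × 0.8 = 0.0160
- variance of change 2 × (0.0222 − 0.0160) ≈ 0.0125
- SE √(0.0125/1057) = 0.34 points

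A 1.5-point trend is then significant about 99% of the time.

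**2. Two baselines.** If success on either counted: 1 − 0.95² = 9.75% for independent tests. With test correlations of 0.5, 0.7 and 0.9 it is about 9.1%, 8.4% and 7.0%.

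**3. Whether a between-arm test fits the planned size** (3 points absolute, p = 0.473)

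Difference in change: SE = √(4v(1 − ρ)/G). Baseline-adjusted: SE = √(2v(1 − ρ²)/G).

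| GPs per arm | ρ | power, difference in change | power, baseline-adjusted |
|---|---|---|---|
| 868 | 0 | 80% | 98% |
| 868 | 0.3 | 92% | 99% |
| 868 | 0.5 | 98% | 99.6% |
| 1057 | 0 | 87% | 99% |
| 1057 | 0.3 | 96% | 99.6% |
| 1057 | 0.5 | 99% | 99.9% |

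The difference in change reaches 90% once ρ is about 0.25 (868 GPs) or 0.08 (1057 GPs).

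**The case against.** The strongest reply is that the sentence is ambiguous. Splitting the pre-post comparisons by group can mean setting the two changes against each other. The research questions, the stated focus of the evaluation and the two-group sample size all point to a between-arm aim, and the analysis section mentions clustering and other factors, so bare mean tests are not the whole plan. The article is condensed, and the exact model may stand in an analysis plan that is not shown.

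Much of this stands. A reader might infer that the arms will be tested separately, each at 5%; the text does not say so. What the reply does not remove is that the one test the article states hangs on the pre-post comparisons, and that the section names no between-arm contrast. Leaving model details to an analysis plan is normal. Wording the tested comparison differently from the design section is a conflict within the article.

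Other inferences should not be drawn:
- **Four tests of the primary outcome (18.5% error).** No text says that both baselines and both post seasons are each tested. The annual measurement defines the outcome, not a testing scheme.
- **No pre-pandemic baseline.** The article says "a period of at least 24 months prior to the start of the intervention will be considered for pre-analysis". That is a minimum and permits a longer period.
- **A quarter mismatch.** "GP claims data from 7 quarters after the start of the intervention are available for analysis", against at least eight before. The influenza rate is annual, and July 2022 to March 2024 covers both autumn-winter periods, so a mean over quarters is not the outcome.

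**Conclusion.** The concern holds as a conflict between the analysis section and the design section over what the 5% primary test compares, together with an unspecified primary baseline. It does not establish that the investigators will rely on within-arm tests.

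If the sentence were followed literally, the consequence would be serious: false significance of about 47% to 96% in the intervention arm for a 1- to 2-point common trend at 868 GPs and ρ = 0.5, or 35% to nearly 100% across the range shown. These figures rest on an assumed base rate, correlation and trend. They illustrate the risk and do not predict it. The 9.75% for two baselines applies only if success on either would count, which the article does not say.

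The between-arm test that the design section promises fits the planned size for a 3-point absolute difference, unless practice rates before and after are nearly uncorrelated and the unadjusted difference in change is used.

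**What to change.** Reword the analysis section to match the design section:

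1. Make one between-arm contrast the single two-sided 5% primary test. One example is the post-intervention influenza rate by arm, adjusted for the practice's own pre-intervention rate. Handle clustering either with a practice random effect in a patient-level model, or with one row per practice and no such effect.
2. Commit to one contrast in advance. Baseline adjustment and the arm-by-period term are not the same analysis. They can differ when the arms differ at baseline, which is plausible because GPs are offered participation after randomisation.
3. Name one primary baseline and one post-period summary.
4. Label within-arm changes as descriptive and the other baseline as a sensitivity analysis.

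The cost is wording and a little extra analysis. The pre-intervention rates come from the same claims data, and no additional GPs are needed. The change should be fixed before the outcome data are analysed.

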### Measures

#### Secondary data collection

The influenza vaccination rate as primary outcome is measured annually for patients insured by a substitute health insurance fund aged 60 and older. The rate will be computed as the fraction of the amount of vaccinated patients insured by a substitute health insurance fund aged 60 and older and all patients insured by a substitute health insurance fund aged 60 and older of the practice under consideration.

The determination of the secondary outcome, vaccination uptake rates for vaccinations recommended by the STIKO for patients aged 60 and older (except for influenza), is more challenging. This is due to the unclear size of the basic population, which, in turn, is a result of the long periods of time between recommended booster vaccinations (the boosters for tetanus, diphtheria, and pertussis are needed/recommended only every 10 years).

If a sufficiently high number of cases is reached, subgroup analyses for different vaccinations are planned (e.g., for pneumococci and herpes zoster).

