***Summative evaluation (secondary and primary data)***			
**Secondary data**: Extract of pseudonymised contract GP billing data according to § 295 SGB V, n = 2114 GPs (n = 1057 GPs each in the intervention and control group) and at full utilisation ≥ 147,980 patients	**Primary outcome**: Influenza vaccination rate **Secondary outcome**: Vaccination uptake rate of the vaccinations recommended by the STIKO for patients aged 60 and older (except for influenza)	-	Descriptive statistics, pre-post comparison (intervention/control group), cluster analysis, subgroup analyses
**Primary data**: Cross-sectional patient survey in intervention practices (n = 50), pre- and post-implementation (2 x n = 1250 patients), paper & pencil survey	**Secondary outcome**: Vaccine literacy	**Further secondary outcome**: HLS19-VAC-DE subscale of the HLS19 instrument (40)	Descriptive statistics, multivariable regression models, multilevel analysis

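### A pre-post change is a poor contrast for vaccinations not normally repeated within the study, and the secondary rate it is applied to has no denominator

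*Protocol article*

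**What the plan says.** Under Data analysis (Secondary data), one analysis serves both billing-data outcomes: "pre-post comparison analyses will be conducted for both outcomes differentiated by intervention and control group". It uses "comparisons of means based on two-sided tests with significance levels of 5" per cent and allows for clustering and unnamed influencing factors.

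Under Summative evaluation: secondary data, the article explains how the non-influenza vaccinations differ. Tetanus, diphtheria and pertussis boosters fall due every 10 years. A repeat against pneumococci after 6 years or more is called beneficial but is not a general recommendation. For the third, "there is no recommendation for a booster vaccination against herpes zoster after the basic immunisation has been completed". The section adds that the data cannot show who was already covered, and concludes: "Therefore, we will analyse the increase in the vaccination uptake rate among participating GPs compared to non-participating GPs".

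Under Measures (Secondary data collection), the influenza rate is annual, with the denominator "all patients insured by a substitute health insurance fund aged 60 and older of the practice under consideration". No denominator is given for the secondary rate. The section says only that it is harder to determine: "This is due to the unclear size of the basic population".

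The Sample section still targets the same 3% increase for the secondary outcome. Because that outcome has the smaller cluster size, it sets the number of GPs.

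**The concern.** For influenza, every patient can be vaccinated both before and after the start, so a pre-post change has a plain meaning. For the other vaccinations, a patient vaccinated in the pre window (at least 24 months) is normally not due again in the seven post quarters. Pre-period uptake is then not a neutral baseline: it removes patients from the pool that can be vaccinated later. Subtracting it penalises whichever group was more active before the start.

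The stated fallback, comparing the increase in uptake between participating and non-participating GPs, still subtracts that baseline, and on a rate whose denominator is not defined. A 3% increase means something different over all patients aged 60 and older than over patients still due. At stake are the size and reading of the secondary effect, on the outcome that drives the sample size.

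**Working it through.** **Inputs from the article.** Share already vaccinated against pneumococci: "vary widely between 14.8% and 40.4% depending on the region in the age group between 60 and 73 years" (Background). Herpes zoster: single digits (Background). Target 3%, unclustered total 17,508, ICC 0.08, cluster size 28 (Sample). Uptake levels below are assumptions, because the article gives none for the secondary outcome.

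**1. The plan's own figures.** Design effect 1 + 27 × 0.08 = 3.16. 17,508 × 3.16 = 55,325 patients. 55,325 / 28 = 1,976 GPs, or 988 per group. Adding 7% (69) gives 1057. These reproduce. The starting 17,508 cannot be traced to a base rate, since none is stated; that does not bear on this point.

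**2. How the baseline feeds into the post rate.** Take a closed cohort and windows of equal length. Let s be the share still due, h the uptake among them, and p = s × h the pre-window rate over all patients. With no intervention effect, the post rate is (s - p) × h = p - p²/s, so the pre-post change is -p²/s.

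**3. Groups alike.** If s and p are the same in both groups, the two changes cancel and the difference in change is 0. The concurrent control does this work.

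**4. Attenuation from patients already vaccinated.** Assume a 3-point gain among patients still due and an all-patient denominator. The observed gain is s × 3:
- pneumococci: 0.852 × 3 = 2.56 points; 0.596 × 3 = 1.79 points
- herpes zoster, 9% assumed already vaccinated: 0.91 × 3 = 2.73 points

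The rate ratio is unchanged if s is equal in both groups.

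**5. Depletion, if rates were formed per year.** The year-2 difference is s × [(1 - h1)h1 - (1 - h0)h0]. With s = 0.596 and uptake of 8% against 5%, year 1 shows 1.79 points and year 2 shows 0.596 × (0.0736 - 0.0475) = 1.56 points.

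**6. Illustration of bias with unequal recent uptake and no intervention effect.** From step 2, the difference in change is -(p1² - p0²)/s:

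| Assumed pre-window uptake | s = 0.852 | s = 0.596 |
|---|---|---|
| 12% vs 8% | -0.0080/0.852 = -0.94 points | -0.0080/0.596 = -1.34 points |
| 10% vs 8% | -0.0036/0.852 = -0.42 points | -0.0036/0.596 = -0.60 points |

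This assumes that both groups have the same already-vaccinated share at the start and that the gap in uptake is recent. If 5% to 10% of patients are replaced by unvaccinated entrants, the 12% vs 8% case gives about -0.8 to -1.1 points. If the gap is long-standing and entrants keep the pool constant, pre equals post in each group and the bias is 0.

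**7. Unequal eligible shares, no intervention effect.** With s = 0.60 against 0.80, and a pool reduced over two pre-years by 0.95² = 0.9025, the difference in change is (0.60 - 0.80) × (0.9025 × h_post - 0.05). For h_post = 0.05 it is +0.10 points; for h_post = 0.08 it is -0.44 points. The sign depends on the background trend.

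**8. Power under attenuation.** The effective size per group is 988 × 28 / 3.16 = 8,754. With s = 0.596 and uptake of 20% rising to 23% among patients still due, the rates are 11.92% and 13.71%. The standard error is √[(0.1050 + 0.1183)/8,754] = 0.00505, and 0.01788/0.00505 - 1.96 = 1.58, so power is 0.94. At 10% uptake it is 0.997. At s = 0.852 it is 0.99 or more.

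**The case against.** The article does not hide the problem. It states the long intervals, the unclear base population and the inability to identify earlier vaccination, and it answers with a concurrent comparison. Step 3 shows that this answer works when the groups are alike. It also says that influencing factors will be considered, which leaves room for pre-period uptake as a covariate. A missing definition alone could be left to a fuller document. All of this stands, and it limits the point.

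Three stronger readings are tempting and are not supported.

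- A reader might infer that the secondary effect is generally biased. That needs the compared groups to differ. Randomisation would not produce the gaps in step 6: at 8,754 effective patients per group, 10% against 8% is about 4.6 standard errors. Self-selection could, because participating GPs accept the offer, complete the training and vaccinate at least 20 patients in the first quarter (Recruitment). The article gives no size for any such difference.
- A reader might infer a serious loss of power by shrinking the 3 points while holding the plan's variance fixed. At the low rates that apply here the variance shrinks too, and step 8 gives 0.94 or more for the pneumococcal range. Only larger assumed coverage lowers it: 0.89 with 50% still due and 0.68 with 30%, both at 20% uptake.
- A reader might infer that vaccinated patients are beyond a second vaccination. The article itself calls a later pneumococcal repeat beneficial, so the accurate wording is that they are normally not due again.

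What the objection does not remove is that the article fixes the contrast and the target: it subtracts a baseline that depletes the pool, and it sizes the trial on a rate without a denominator.

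**Conclusion.** The point holds in limited form. The pre-post comparison set for both outcomes suits influenza and is a poor contrast for the long-interval or once-only vaccinations. With similar groups the consequence is attenuation: 3 points among patients still due become 2.56 to 1.79 points for pneumococci and about 2.7 for herpes zoster, if the denominator is all patients, which is an inference. Bias in either direction is possible only if pre-period uptake or eligible shares differ between the compared GPs. The -0.4 to -1.3 points are an illustration under assumed, recent differences in uptake, not an expected value. The undefined denominator is the firmest fault, because the 3% target and the 1057 GPs per group depend on it. Since this is a secondary outcome, it should be corrected but does not threaten the primary analysis.

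**What to change.** For each non-influenza vaccination, replace the pre-post change by a between-group comparison of cumulative uptake over the whole post period.

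- **Numerator:** patients with at least one billed vaccination of that type from 01.07.2022 to 31.03.2024, each counted once.
- **Denominator:** the practice's substitute-fund patients aged 60 and older, minus those with that vaccination billed in the pre-period claims, if patients can be linked across quarters; otherwise all such patients. Apply the same rule in both groups.
- **Model:** enter the practice's pre-period uptake as a covariate instead of subtracting it, and account for clustering by practice.
- **Target:** restate the 3% as percentage points in this denominator.

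The cost is a change of analysis wording and some programming on claims already planned. Linkage must be confirmed: the article says that GPs are followed in pseudonymised form over all quarters but does not say so for patients. The count-once rule also needs linkage within the post period. Vaccinations before the claims window stay unseen, so some dilution remains, and a covariate does not remove self-selection of participating GPs.

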#### Summative evaluation: secondary data

The secondary data analysis is based on data on vaccination rates before and after the intervention, which will be compared between intervention and control group and will address the following research questions:

Does the intervention lead to an increase in influenza vaccination uptake rates in the GP practices among persons insured by one of the six substitute health insurance funds aged 60 and older (primary outcome) group?Does the intervention lead to an increase in the vaccination uptake rate for the other vaccinations recommended by the STIKO for persons aged 60 and older (seasonal influenza, pneumococci, herpes zoster, and revaccinations against tetanus, diphtheria, and pertussis) (secondary outcome)?Since previous analyses of vaccination activity have shown significant regional differences in vaccination uptake rate [28], do the effects in (1) and (2) vary between the participating regions of Westphalia-Lippe, North Rhine and Schleswig-Holstein?

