### Recruitment

The recruitment of GPs for study participation takes place three months prior to the start of the intervention phase by the three participating regional Associations of Statutory Health Insurance Physicians (ASHIP) Schleswig-Holstein, North Rhine and Westphalia-Lippe, considering the available contingent of participants in their region. In Germany, the ASHIP are bodies under public law, which represent all physicians and psychotherapists treating compulsory insured patients. First, all potentially eligible GPs in the three regions, meaning GPs participating in primary care according to § 73 (1a) SGB V (excluding paediatricians), who have vaccinated patients aged 60 and older insured by the substitute health insurance fund in the past, will be identified. Substitute health insurance funds are a type of health insurance fund with the largest percentage of insured persons on the German market. There are no other major differences between this and other types of health insurance funds. Subsequently, these GPs will be stratified by the three ASHIPs, and randomised into two groups (intervention/control). The potential participating GPs in the intervention group will be contacted by the responsible ASHIP and receive the offer to participate in the intervention group. It is pointed out that participation in the intervention is also associated with participation in the accompanying evaluation study. Subsequently, all enrolled GPs, as well as at least one medical assistant from the practice, complete the online training that is completed after an online knowledge test and submit the certificate of successful participation to the associated ASHIP.

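### Research question 3 asks whether the intervention effect differs between regions, but the regional analysis stated compares uptake rates, which is a different quantity

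*Protocol article*

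**What the plan says.** Under Summative evaluation: secondary data, the protocol article lists three research questions. The first is "Does the intervention lead to an increase in influenza vaccination uptake rates in the GP practices", for insured persons aged 60 and older; the second asks the same of the other recommended vaccinations. The third is "do the effects in (1) and (2) vary between the participating regions of Westphalia-Lippe, North Rhine and Schleswig-Holstein". Its stated motivation is that "previous analyses of vaccination activity have shown significant regional differences in vaccination uptake rate".

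Under Data analysis, Secondary data, the main analysis is by arm: "pre-post comparison analyses will be conducted for both outcomes differentiated by intervention and control group". The section says that clustering and various unnamed influencing factors will be allowed for. The regional analysis comes last and is conditional: "if a sufficiently high number of cases in all regions is reached", then "a comparing analysis of the vaccination uptake rates between the three regions will be conducted". Table 1 adds only the general entry of subgroup analyses for the secondary data.

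Under Recruitment, eligible GPs are identified in the three regions, and then "these GPs will be stratified by the three ASHIPs" and randomised to intervention or control.

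**The concern.** Question 3 concerns effect modification: does the increase caused by the intervention differ by region? The analysis sentence concerns levels: do the uptake rates differ by region? The article itself reports that levels are already known to differ, so a finding that they differ again would say nothing about where the intervention worked better or worse.

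This goes beyond detail left to an analysis plan. The article does state a regional analysis, and the quantity it names is not the one in the question. The Discussion says the results will inform a decision on adopting the intervention into standard care in Germany. A regional difference in rates could be taken there for a regional difference in effect, or a real difference in effect could go unreported.

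**Working it through.** **Side by side**

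| | Research question 3 | Regional analysis as stated |
|---|---|---|
| Quantity | effect on uptake, as in questions 1 and 2 | uptake rate |
| Contrast | intervention against control, pre to post, compared across regions | region against region |
| Arm mentioned | yes, through questions 1 and 2 | no |

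The article gives no figure for the regional analysis, so there is none to reproduce. What follows shows how far the two quantities can diverge and how precise the right comparison would be.

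**Inputs from Sample**
- ICC 0.08 and cluster size 48. The stated design effect reproduces: 1 + (48 − 1) × 0.08 = 4.76.
- 1057 GPs per group.
- Assumed increase of 3%, read here as percentage points; two-sided alpha 5%; power 90%.

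**Assumptions of mine**
- Three regions of equal size, and rates near 50%.
- A post-period comparison of proportions. The article gives no pre-post correlation, so any change in precision from using baseline data is left out.

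**Standard errors**
- Effective patients per arm: 1057 × 48 / 4.76 = 10,659.
- Overall effect: SE = sqrt(2 × 0.25 / 10,659) = 0.685 points.
- Effect within one region: sqrt(3) × 0.685 = 1.186 points.
- Difference in effect between two regions: sqrt(2) × 1.186 = 1.678 points.
- Mean rate of one region, arms pooled: variance = 1.186² / 4 = 0.352.

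**Identical effect in every region, different regional levels.** The test of equal rates has 2 degrees of freedom and noncentrality equal to the sum of squared deviations of the regional rates divided by 0.352. With evenly spaced rates:

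| Span of regional rates | Noncentrality | P(reject equal rates) | P(reject equal effects) |
|---|---|---|---|
| 2 points | 2 × 1² / 0.352 = 5.7 | 0.56 | 0.05 |
| 5 points | 2 × 2.5² / 0.352 = 35.5 | >0.99 | 0.05 |
| 10 points | 2 × 5² / 0.352 = 142 | 1.00 | 0.05 |

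**Different effects, hidden by levels.** Take effects of 0, 3 and 6 points and baselines of b, b − 1.5 and b − 3. With equal arms, the pooled regional rate is baseline plus half the effect: b + 0, b − 1.5 + 1.5 and b − 3 + 3, which is b in all three. The test of equal rates then rejects only at its nominal 5%. The test of equal effects has noncentrality 2 × 3² / 1.186² = 12.8 and power of about 0.90. For effects of 1.5, 3 and 4.5 points, the noncentrality is 2 × 1.5² / 1.186² = 3.2 and the power about 0.34.

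**Detectable difference in effect between two regions (80% power, multiplier 1.960 + 0.842 = 2.80)**
- Planned numbers: 2.80 × 1.678 = 4.7 points.
- Overall analysis with exactly 90% power for 3 points: overall SE = 3 / 3.2415 = 0.93; sqrt(6) × 0.93 = 2.27; 2.80 × 2.27 = 6.4 points.

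Both exceed the assumed overall effect of 3 points.

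**The case against.** The best reply is that the sentence is shorthand. The lead-in to the research questions says that rates before and after the intervention, compared between the groups, will address all three of them. The regional sentence closes a section on by-arm, pre-post analyses, and vaccination uptake rate is the article's own name for its outcome. On that reading the by-arm result is what will be compared across regions, and the remaining detail belongs in an analysis plan that is not shown. This is possible, and it rules out saying that the analysis is certain merely to reproduce known differences. It does not remove the point: neither the analysis section nor Table 1 says that effects are compared by region, and the sentence names rates.

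Three stronger inferences might tempt a reader, and the document does not support them.

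- **The pneumococcal range as proof.** The Background says that these rates "vary widely between 14.8% and 40.4% depending on the region". That range is for Germany, for ages 60 to 73, and for a secondary outcome. It is not given for the three study regions and does not show what a rate comparison among them would find.
- **A main standard error that is materially too large.** The analysis section does not name the stratum, but its unnamed influencing factors could include region. Stable regional differences in level also largely cancel in a pre-post contrast. No size for any loss can be derived.
- **The case-number condition as an error.** Making a regional comparison conditional on numbers is a defensible choice, even with no threshold given.

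**Conclusion.** The mismatch is real and worth correcting. The question concerns effects, and the only stated regional analysis, followed literally, concerns rates and does not answer it. It can reject when effects are equal (probability about 0.56 for a 2-point span in regional rates and above 0.99 for 5 points) and can stay at 5% when effects range from 0 to 6 points. These are illustrations resting on equal regions, rates near 50%, full enrolment and the plan's own design effect; the article gives no rates for the three regions.

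The right comparison is feasible because randomisation is stratified by region and billing data exist for both arms. It will be imprecise, with a smallest detectable pairwise difference of about 4.7 to 6.4 points, so a non-significant interaction should not be read as equal effects. The point is confined to question 3 and does not call the main between-arm comparison into question.

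**What to change.** - Restate the regional analysis as a comparison across regions of the pre-post, intervention-versus-control effect, using a region-by-arm interaction in a model that accounts for clustering by practice.
- Report the effect in each region with its confidence interval, and state the limited precision (about 4.7 to 6.4 points for a pairwise difference, with the assumptions behind each figure).
- Include ASHIP, the randomisation stratum, as a factor in the between-arm analyses of both outcomes.
- If the present sentence was already meant this way, naming effects in place of rates is enough to align it with question 3.

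The cost is one model term and two sentences. No extra data or recruitment is needed, and the case-number condition can stay.
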